### Recruitment {15}

Patients are recruited from University Hospital for Cardiac Surgery, Medical University of Innsbruck, Innsbruck, Austria, starting in November 2018. No specific measurements will be taken. Given the structure of the Austrian health care system, this department is the only institution in the allocated region providing cardiac surgery. All patients with a reduced LVEF admitted to CABG surgery, as decided by the institutional heart team, will be screened for eligibility by the study investigators. The approximate recruitment rate is expected to be 20 patients per year.

## Assignment of interventions: allocation

### Sequence generation {16a}

The investigational medicinal product (shockwave therapy) to which individual patients will be assigned is determined by a randomized schedule with a 1:1 allocation ratio. The sequence allocation will be generated in permuted blocks by an independent statistician. The Competence Centre for Clinical Trials at the Medical University of Innsbruck will have access to the allocation sequence to prepare the individual opaque envelopes for each participant.

### Concealment mechanism {16b}

The randomization process will be realized independently from the clinical investigators using opaque envelops (fully blind randomization) For each participant enrolled on the study, one envelope will be opened at the end of the CABG procedure after opening the aortic clamp (bypasses fully established) while the patient is still connected to the heart-lung machine to get group allocation information.

### Implementation {16c}

SPIRIT guidance: Who will generate the allocation sequence, who will enrol participants, and who will assign participants to interventions.

An independent statistician from an external company will provide the randomization list. The opaque envelopes will be prepared by the Clinical Trials Monitoring Center of Innsbruck Medical University.

A participant can be included by every member of the research team; when in doubt, the inclusion will be judged by the whole research team and reviewed by the clinical trial monitoring board anyways.

## Assignment of interventions: blinding

### Who will be blinded {17a}

This study is single-blinded as the PI, and the surgical personnel involved in the study procedure (shockwave therapy or sham treatment) know the randomization arm. However, all study assessments will be performed in an observer-blinded fashion. Patients, the investigators performing the endpoint analyses, and data analysts are blinded to the group assignment.

### Procedure for unblinding if needed {17b}

Unblinding is not applicable in this study as no continuous study intervention (e.g. medication) is used but a single intra-operative treatment. Documentation and processing of device-related adverse events do not require unblinding.

## Data collection and management

### Plans for assessment and collection of outcomes {18a}

#### Data collection and management

Baseline, outcomes and other trial data will be collected by the study investigators. Monitoring and audits will be performed for quality assurance within the clinical investigation. Monitoring and auditing procedures developed or endorsed by the Sponsor will be adhered to, in order to comply with EN ISO 14155 guidelines and local legal requirements to ensure the acceptability of the study data. Regulatory authorities, the ethics committees, and Sponsor’s delegates may perform on-site inspections or audits, for which the Investigator must provide support at all times. All collected data of this study have to be recorded in the CRF by appropriate authorized persons. This is also valid for data of patients, who dropped out of the study. Further details on data entry and handling are specified in section 19.

#### Study-specific training

All investigators will be trained within the Initiation Visit. Training topics cover Good Clinical Practice, the study protocol, and the operation of the DSP-002 Flashwave MMC and the Cardiac Shockwave Probe (CSP). The training will be documented on a specific training log and the respective delegations will be documented on the Delegation Log Form. No specific surgical skills are needed for the application of DESWT with the Cardiac Shockwave Probe. Details about the application are provided in section 11.

#### Medication

Throughout the study, investigators are permitted to use their clinical judgement when prescribing concomitant medications and treatments for trial patients. Local prescribing information and institutional guidelines should be followed as applicable.

#### Optimized, guideline-directed medical therapy

This study is designed to be an all-comers study. Optimized medical therapy according to the European Society of Cardiology Guidelines for the diagnosis and treatment of acute and chronic heart failure may already be achieved at the time of screening and treatment or not. At the time of follow-up visits to assess LVEF via cardiac MRI (D180, D360) patients have to be on stable, guideline-directed medical therapy for at least 30 days prior to each visit. This includes the following definitions according to the patients’ clinical presentation and the judgement of the responsible physician:No more than a 100% increase or a 50% decrease of the dosage of any one medication other than a diuretic.Medication changes within a drug class are allowed as long as the equivalent dosage is within the limits specified above.

#### Cardiac MRI

All CMR examinations will be performed on a 1.5-T clinical MR imaging unit (AVANTO_fit; Siemens, Erlangen, Germany) according to a multiparametric protocol including the following sequences:

Cine-SSFP: Cine CMR images in short-axis slices covering LV cavity and in long-axis slices (2-, 3- and 4-chamber view) will be acquired using a breath hold, retrospective ECG-triggered steady-state free-precession (SSFP) trueFISP bright-blood sequence with the following typical imaging parameters: Voxel size = 1.5 × 1.5 × 6 mm^3^, echo time = 1.13 ms, time to repetition = 38.92 ms, flip angle = 80°, parallel imaging mode: generalized auto-calibrating partially parallel acquisition (GRAPPA), acceleration factor = 2.Late enhancement CMR images will be acquired by using an ECG-triggered phase-sensitive inversion recovery (PSIR) single-shot TrueFISP sequence with consecutive short-axis slices 10 min after an intravenous administration of 0.15 mmol/kg of Gd-DO3A-butriol (GadovistTM, Bayer Vital, Leverkusen, Germany) at 2 ml/s, followed by 20 ml of saline flush, administered using an automatic injector (Spectris Injection System, Medrad, Pittsburgh, USA) with the following typical imaging parameters: voxel size = 1.4 × 1.4 × 8 mm^3^, echo time = 1.22 ms, time to repetition = 945.60 ms, flip angle = 45°.Mapping sequencesT1 Mapping: A single breath-hold, ECG-gated short modified Look-Locker inversion recovery (shMOLLI) sequence will be acquired on a LV basal, mid-ventricular and apical short-axis slice at end-diastole before and 20 min after contrast media administration. Typical imaging parameters are voxel size = 1.4 × 1.4 × 8 mm^3^, four single shot balanced SSFP readout trains with effective inversion times between 424 and 1439.36 ms, echo time = 1.13 ms, time to repetition = 359.84 ms, flip angle = 35°, parallel imaging mode GRAPPA with an acquisition factor of 2, and slice thickness = 8 mm. A motion correction algorithm will be applied to allow for movement artefacts.T2 Mapping: T2 quantification will be performed for characterization of myocardial oedema. Three matching short-axis T2-weighted images will be obtained before administration of contrast media using a free-breathing, ECG-gated, T2-prepared trueFISP sequence at 0, 25, and 55 ms, allowing generation of the T2 time for each individual voxel. Again, a motion correction algorithm will be applied to allow for movement artefacts. Typical imaging parameters are: echo time = 1.06 ms, repetition time = 187.37 ms, flip angle = 70°, bandwidth = 1184 Hz/pixel, matrix = 192 × 112 pixels, spatial resolution = 2.0 × 2.0 × 8.0 mm, and slice thickness = 8 mm.T2* Mapping: Myocardial haemorrhage will be assessed by T2* quantification using a breath-hold, cardiac gated gradient echo sequence with 8 echoes obtained in three matching short-axis slices before administration of contrast media. Again, a motion correction algorithm will be applied to allow for movement artefact. Typical imaging parameters are echo time = 2.02–16.3 ms, time to repetition = 948.8 ms, flip angle = 20°, bandwidth = 814 Hz/pixel, matrix = 256 × 110 pixels, spatial resolution = 1.6 × 1.6 × 8.0 mm, and slice thickness = 8 mm.Postprocessing analysisCine-SSFP: Left ventricular (LV) volumes, LV myocardial volume and mass as well as LV ejection fraction (EF) will be analysed via standard software (Circle Cardiovascular Imaging, Calgary, Canada) for postprocessing analyses with semi-automatic detection of LV endo- and epicardial contoursLate enhancement: Infarct characteristics (infarct location, infarct size, infarct transmurality, microvascular obstruction) will be determined as myocardial areas with signal intensity above the average of apparently normal myocardium in the opposite noninfarcted myocardial segments plus 5 standard deviations. Planimetry of late enhancement areas will be performed on IMPAX EE workstation (Agfa Healthcare, Bonn, Germany).Mapping sequences: Motion-corrected, colour-coded T1 native -, T1 post contrast -, T2 - and T2*- myomaps will be automatically inline generated by fitting signal intensities at each image pixel with an exponential model for the given echo times. Evaluation of the maps will be carried out on IMPAX EE workstations (Agfa Healthcare, Bonn, Germany) and performed by manually outlining endo- and epicardial contours with taking care to exclude subendocardial blood and subepicardial tissue to avoid partial volume effects.LV myocardium will subsequently be divided into regions of interest (ROI): infarct core, peri-infarct zone and remote myocardium, defined as the segment contralateral to the infarct segment, by drawing manual contours over the corresponding maps and visually inspecting viability on late enhancement images. Extracellular volume (ECV) values will be generated using a previously established equation. R1 will be defined as 1/T1 and delta will be defined as the difference between native and post-contrast T1 values. T2 maps (ECG-gated, T2 prepared trueFISP sequence at 0, 25, and 55 ms in matching slices before administration of contrast media) and T2* maps (ECG-gated gradient echo sequence with 8 echoes) will be obtained in matching slices before administration of contrast media.

#### Laboratory analysis

Samples of laboratory tests will be analysed at the local laboratory.

Blood analysis will be done as part of the regular safety assessments at baseline, at hospital discharge and at visits in the long-term follow-up.

The following parameters will be measured:Laboratory results general:LactatdehydrogenaseErythrocytesHaemoglobinHaematocritPlatelet countCRPLeukocytesThrombo testActivated partial thromboplastin timeInternational normalized ratioPro BNPLaboratory results heart enzymes:Total CKCK-MBCK-MB %Troponin T

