### Eligibility criteria {10}

Adult patients with postischemic heart failure undergoing coronary artery bypass grafting (CABG). All participants will undergo the usual standard medical work-up before, during, and after CABG according to the ESC/EACTS Guidelines on Myocardial Revascularization. This includes Coronary Angiography, Echocardiography, Spirometry, Carotid Artery Duplex Scan, Cardiac MRI, Computed Tomography, and interviews with the Cardiologist, Cardiac Surgeon, and Anesthesiologist.

Inclusion criteria:Male or female patients above 21 and under 90 years of age undergoing primary coronary artery bypass grafting.Patients have to present with reduced left ventricular function defined as LVEF ≤ 40%.Patients have to present with regional left ventricular wall motion abnormalities.Patients have to give written informed consent to participate in the study.

Exclusion criteriaSignificant concomitant aortic valve disease in need of surgical treatment (Except significant aortic valve disease not detected in preoperative cardiac ultrasound that is detected intra-operatively).Serious radiographic contrast allergy.Patients in cardiogenic shock or presenting with acute myocardial infarction (STEMI or NSTEMI)Patients with a contraindication for cardiac MRI (e.g. glomerular filtration rate <30ml/min/1.73m^2^)History of significant ventricular arrhythmias, except arrhythmias associated with MI.Present co-morbidity, which reduces life expectancy to less than 1 year.Presence of ventricular thrombus.Presence of a cardiac tumour.Pregnancy.

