### Outcomes {12}

Primary endpoints:Efficacy: Improvement in LVEF measured by cardiac MRI from baseline to 360 days.Safety: Occurrence of device-related complications (adverse device effects or serious adverse device effects) within 360 days.

Secondary endpoints:Endpoints related to the efficacy are changes in the following parameters within a time frame of 360 days:6-min walk test distanceNYHA functional classSerum nt-proBNP levelsRenal function, measured by glomerular filtration rate (GFR)Seattle Angina Pectoris Questionnaire (SAQ)36-item short-form survey (SF36)Minnesota Living with Heart Failure Questionnaire (MLHFQ)Secondary safety-related endpoints include the following observations within a time frame of 6 days:Occurrence of ventricular arrhythmia during the hospital stayOccurrence of device-related peri-operative myocardial damage detected by a rise of cardiac biomarkers: creatine kinase (CK-MB) and troponin T (TropT)Occurrence of signs of device-related infection detected by a rise of C-reactive protein (CRP) or leukocytosis during the hospital stay

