### Plans for collection, laboratory evaluation and storage of biological specimens for genetic or molecular analysis in this trial/future use {33}

#### Biosamples

At the scheduled visit, blood specimens and urine samples should be collected, whereas fasting is not required. The specimens will be forwarded to the cardiosurgical research laboratory in a pseudonymous manner, which will perform the analysis.

Data arising from clinical genotyping will be subject to the confidentiality standards.

Blood and urine samples will be taken during screening, 4–12h post-surgery, 48–52h post-surgery, day 90 and day 360.

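### The only schedule tied to CK-MB, troponin T, CRP and leukocytes does not match the 6-day and in-hospital safety endpoints that depend on them

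*Protocol article*

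**What the plan says.** The Outcomes section {12} introduces three safety endpoints in one sentence: "Secondary safety-related endpoints include the following observations within a time frame of 6 days". Two of them rest on blood markers. One is peri-operative myocardial damage attributed to the device, shown by rising CK-MB and troponin T. The other is device-related infection, shown by rising CRP or by leukocytosis while the patient is in hospital.

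The Laboratory analysis section, under {18a}, lists total CK, CK-MB, CK-MB %, troponin T, CRP and leukocytes among its parameters. It says that blood analysis is part of the regular safety assessments and is done "at baseline, at hospital discharge and at visits in the long-term follow-up". It adds: "Samples of laboratory tests will be analysed at the local laboratory".

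The Biosamples section, under {33}, gives a different set of times: "Blood and urine samples will be taken during screening, 4–12h post-surgery, 48–52h post-surgery, day 90 and day 360". It sits under the heading on specimens for genetic or molecular work and continues: "The specimens will be forwarded to the cardiosurgical research laboratory in a pseudonymous manner". It names none of the four markers.

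Two other places touch on routine data. Eligibility criteria {10} states: "All participants will undergo the usual standard medical work-up before, during, and after CABG", with no marker times. The section on adverse events and harms {22} lists review of medical records and laboratory data as one way of finding adverse events.

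**The concern.** Shock waves are applied directly to the heart, so acute myocardial injury is a main safety question. Both arms have on-pump CABG, so a device effect would appear as a difference between arms. That comparison needs values taken at the same post-operative times. A discharge sample does not provide this, because its time depends on when each patient leaves hospital.

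The adverse event definition may not catch what this endpoint misses. It counts an abnormal laboratory value only if the value causes signs or symptoms, is judged clinically significant, or needs therapy. An isolated enzyme rise can therefore fall outside the primary safety endpoint, and the biomarker endpoint is then the planned place to see it. If that endpoint were read from discharge values, a small rise in both arms could be reported as no device-related damage.

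**Working it through.** The plan gives no figure to reproduce. The check counts the stated post-operative blood draws that fall inside the endpoint window.

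**Inputs**
- Endpoint window: 6 days (Outcomes {12}), taken here as counted from surgery, which is an assumption. 6 × 24 = 144 h.
- Draws tied to the markers: baseline, discharge and long-term visits (Laboratory analysis).
- Other post-operative draws: 4–12 h, 48–52 h, day 90 and day 360 (Biosamples).
- Discharge day: not stated, so both cases are shown. Discharge is assumed to come after 52 h.

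**Which draws fall in the window**
- Baseline is before surgery and supplies only the reference value.
- Discharge counts if it is on or before day 6, and otherwise does not.
- The follow-up days that the article names are 90, 180 and 360, all outside the window.
- The later early biosample window ends at 52 / 24 = 2.17 days, so both early biosample draws are inside.

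| Draws counted | Discharge on or before day 6 | Discharge after day 6 |
|---|---|---|
| Laboratory analysis schedule | 1 | 0 |
| Biosamples schedule | 2 | 2 |
| Both | 1 + 2 = 3 | 0 + 2 = 2 |

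Between surgery and discharge, the Laboratory analysis schedule has 0 draws and the Biosamples schedule has 2.

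For CRP and leukocytes, the item itself refers to the hospital stay. On that reading the discharge value counts whatever the day, which gives one value at the very end of the stay. Under the 6-day lead-in the count is again 1 or 0.

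**Side by side.** The section that names the markers has no early draw. The section that has early draws does not name the markers and sends its samples to a different laboratory. The endpoint needs both, and no sentence in the article joins them.

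**The case against.** A reader might infer that no blood is taken between baseline and discharge, and that a biomarker rise therefore cannot be detected. The documents do not support that, for these reasons:

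- The Biosamples section schedules two early post-operative draws.
- The Laboratory analysis section does not say that its times are the only ones used, or that the endpoint is read from the discharge sample.
- A discharge value can still lie above baseline.
- Routine work-up after CABG and the review of laboratory data for adverse events may supply in-hospital values.
- The participant timeline {13} is not shown. The article is also condensed, so the timeline or the full protocol may list early marker draws.

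The impact is also limited. This is a secondary endpoint, summarised descriptively with exploratory tests only. Recruitment closed on 01.06.2022, so no sampling can be added.

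All of this narrows the point but does not remove it. The article is not silent on marker timing: it states a schedule, and that schedule does not fit the endpoint. The biosamples are not linked to the markers, and the references to routine data give no times. If the timeline does list early marker draws, the Laboratory analysis text is at odds with it and still needs correcting.

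**Conclusion.** The mismatch is real and is one of reconciliation. As stated, the schedule tied to CK-MB, troponin T, CRP and leukocytes yields at most one post-operative value in the 6-day window, and none if discharge is after day 6. Two early draws that would suit the endpoints are scheduled but not connected to them.

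The count rests on two assumptions: the 6 days run from surgery, and discharge comes after 52 h. It needs no assumption about how fast the markers rise and fall. The further judgement, that the schedule is poorly suited to an early rise, assumes that such a rise may have partly or wholly subsided by discharge. The documents give no figures on this, so no loss of sensitivity is quantified. Nothing here shows that early values were not collected. It shows only that the text does not say which values define the endpoints.

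**What to change.** Reconcile the Outcomes, Laboratory analysis and Biosamples sections before the database closes. The last visit was expected in April 2023. People blinded to allocation should settle the definition, which should state that:

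- both endpoints are derived from CK-MB, troponin T, CRP and leukocyte values in the 4–12 h and 48–52 h windows, compared with baseline, by the same rule in both arms;
- the values come from routine hospital laboratory records or, where still available, from stored samples, with the source and actual time recorded;
- the numbers missing and off-time are reported by arm;
- discharge values may be shown, but are not taken alone as evidence that there was no device-related myocardial damage.

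If the participant timeline or the full protocol already lists early marker draws, correct the Laboratory analysis text to agree with it.

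The cost is a wording change and record extraction. With the planned 80 patients this is at most 80 × 2 × 4 = 640 post-operative values; the number actually enrolled is not stated. The downside is that some values will be missing or outside the windows, and the Biosamples section does not say that any samples remain for these assays.

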#### Echocardiography

Echocardiography has become routinely used in the diagnosis, management, and follow-up of patients with any suspected or known heart diseases. It is one of the most widely used diagnostic tests in cardiology. It can provide a wealth of helpful information, including the size and shape of the heart (internal chamber size quantification), pumping capacity, and the location and extent of any tissue damage. An echocardiogram can also give physicians other estimates of heart function, such as a calculation of the cardiac output, ejection fraction, and diastolic function. The echocardiography will be performed according to the routinely performed assessment protocol transthoracic, but during surgery transoesophageal.

#### Six-min walk test

The 6-min walk test is a sub-maximal exercise test used to assess aerobic capacity and endurance. The distance covered over a time of 6 min is used as the outcome by which to compare changes in performance capacity. The test will be performed indoors along a long, flat, straight, enclosed corridor with a hard surface without a warm-up period after a rest of 10 min, while the patient is sitting in a chair located near the starting position. Thereafter we have the patient stand and rate his/her baseline dyspnoea and overall fatigue using the Borg scale. The patient has to be instructed to walk as far as possible for 6 min without running of jogging. To measure time and walking distance, a timer and a lap counter are used. While walking the patient should be informed every minute how long he has to go. After the test, the postwalk dyspnoea and fatigue levels will be recorded. Blood pressure and heart rate will be measured at baseline and postwalk. Resting during the test is allowed, but time keeps running. The test will be stopped, if the patient develops chest pain, intolerable dyspnea, staggering, diaphoresis, intolerable cramps, and/or an ashen appearance.

